### Procedure

Students who are interested in enrolling in the study will contact the study team through a contact form from a student mental health platform (i.e., on  www.studicare.com) or directly via email. If participants satisfy inclusion criteria they will be randomly assigned to either the IG or the WLC. Students who are assigned to the IG can initiate the online-based self-help intervention immediately after randomization. Students in the WLC will receive access to the program six months after randomization. The study includes three assessments: both groups are assessed at baseline (t0), immediately after completing the program (t1; 10 weeks) and at follow-up six months after randomization (t2). The assessment at t1 (10 weeks) is independent from treatment completion. Treatment adherence will be monitored after t1. Self-reported measures are collected using a secure web-based assessment system (UNIPARK, 256-bit encrypted [60]). This system allows for data validation (range checks, double data entries) to improve data quality. Additionally, participants’ SAD symptoms in IG will be assessed weekly via the intervention platform. The collected data will be stored securely.

### Measurements

A detailed overview of all measures at baseline (t0), 10-week post-treatment (t1) and 6-month follow-up is given in Table 2.

**Table 2 Tab2:** Measurements and time of assessment

Instrument	Abbreviation	Aim	Time of assessment		
			t0	t1	t2
Clinician administered					
Structured Clinical Interview for DSM-IV Axis I Disorders	SCID-I	DSM-IV Axis I disorders	✔		✔
Self-report ratings					
Primary Outcome Measure					
Social Phobia Scale^a^	SPS	Symptoms of SAD	✔	✔	✔
Social Interaction Anxiety Scale^a^	SIAS	Symptoms of SAD	✔	✔	✔
Secondary Outcome Measure					
Liebowitz Social Anxiety Scale	LSAS-SR	Social anxiety symptoms	✔	✔	✔
Beck Depression Inventory II	BDI-II	Symptoms of depression	✔	✔	✔
Brief Symptom Inventory	BSI	Psychiatric symptoms	✔	✔	✔
Inventory of Interpersonal Problems	IIP-64	Interpersonal problems	✔	✔	✔
Fear of Positive Evaluation Scale	FPES	Fear of positive evaluation	✔	✔	✔
Disqualification of Positive Social Outcomes Scale	DPSOS	Fear of positive evaluation	✔	✔	✔
EuroQol (EQ-5D-5 L)	EQ-5D-5 L	Quality of life	✔	✔	✔
Assessment of Quality of Life (AQol)	AQoL-8D	Quality of life	✔	✔	✔
Client Satisfaction Questionnaire	CSQ-8	Client satisfaction			
Trimbos/iMTA Questionnaire for Costs associated with Psychiatric Illness	TiC-P	Cost-effectiveness	✔		✔
Credibility Expectancy Questionnaire	CEQ	Treatment expectancy			

t0 Baseline; t1 10 weeks; t2 6 months; Assessments ✔ = intervention and control group;  = intervention group ^a^ process measures assessed every 2 weeks

### Primary outcome measures

#### Symptoms of SAD

The primary outcome is SAD symptoms. SAD symptoms will be measured with two widely used measures, the Social Phobia Scale and the Social Interaction Anxiety Scale (SPS & SIAS; [61]). These two self-report questionnaires complement one another and are usually administered together. The SIAS assesses more general fears of social interaction (e.g., “I tense up if I meet an acquaintance in the street”), while the SPS focuses on fears of being judged by others during daily activities (e.g., “I become anxious if I have to write in front of others.”). Both scales consist of 20 items to be rated on a 5-point Likert scale (0= “not at all” to 4 = “extremely”). These two companion measures have been found to be valid, reliable and useful for clinical and research purposes [62]. Cronbach alphas for the SIAS and SPS range from 0.90 to 0.94 [63].

### Secondary outcome and process measures

#### Diagnostic status

The diagnostic status will be assessed with the Structured Clinical Interview for DSM-IV (SCID-I [64]). The interview will be conducted and recorded by trained raters (clinical psychologists or graduate students in psychology) via telephone at baseline and 6-months. The raters are blind to the condition the participants are assigned to. In order to ensure blinding, (a) participants receive information on the importance of not informing interviewers about the conditions they were assigned to, (b) raters receive a written reminder to not ask the participants for their randomization status, (c) written and verbal reminders for the participants before the interview; and (d) a documentation after the interview if the rater is still blind to treatment condition. The inter-rater reliability will be evaluated through a random selection of 10% of recorded cases.

#### Beck depression inventory II

Depression severity will be assessed using the Beck Depression Inventory II (BDI-II) [65]. The scale consists of 21 items each rated on a 4-point Likert-scale. Prior research has shown high reliability and validity in SAD clients [27].

#### Brief symptom inventory

General psychopathology will be assessed using the Brief Symptom inventory (BSI), which spans 9 dimensions, including insecurity in social situations, anxiety, depressiveness and compulsivity [66]. The BSI assesses symptoms within the past week and has shown robust psychometric properties [67]. The Global Severity Index (GSI), the overall mean score, will be reported.

#### Liebowitz social anxiety scale

The Liebowitz Social Anxiety Scale (LSAS) [68, 69] is a self-report scale that assesses fear and avoidance in 24 different situations. Thirteen of the situations relate to performance and the remaining items assess situations within the context of social interactions. Prior research has shown good to excellent reliability and validity (Cronbach’s alphas ranging from 0.83 to 0.94) [68].

#### Inventory of interpersonal problems

Difficulties in interpersonal behavior and sources of relational distress will be assessed using the Inventory of Interpersonal Problems (IIP-64) since they indicate assertiveness and passivity of participants. The instrument has eight dimensions and has shown adequate psychometric properties (Cronbach’s alphas ranging from 0.71 to 0.82) [70, 71].

#### Fear of positive evaluation

Fear of positive social feedback will be assessed using the Fear of Positive Evaluation Scale [72]. The FPES is a self-report measure consisting of 10 items and has shown good psychometric properties in clinical and healthy samples [48, 72].

The disqualification of positive social outcomes (DPSO) is a cognitive strategy which has been linked to FPE [43, 72]. This cognitive tendency is proposed to serve as a mental safety behavior in the context of FPE and will be measured using the Disqualification of Positive Social Outcomes Scale (DPSOS) [73]). The DPSOS is designed to measure the disqualification of positive outcomes on two dimensions, other-oriented attributions (e.g., “people will laugh at my jokes even if they are not funny”) and self-oriented attributions that refer directly to DPSO (e.g., “I frequently dismiss my own social successes and accomplishments”).

#### Quality of life

The Assessment of Quality of Life (AQol) [74] and the EuropeanQuality of Life 5 Dimensions 3 Level (EQ-5D-5L) instrument [75, 76] will assess quality of life. The AQol assesses eight dimensions (independent living, pain, senses, mental health, happiness, coping, relationships, self-worth) and allows for the calculation of separate sum scores for each dimension. The EQ-5D is a widely applied, valid and reliable measurement of quality of life. It consists of five items on a five-point Likert scale related to mobility, self-care, common activities, pain/discomfort and anxiety/depression. Additionally, this measure contains a visual analogue scale (VAS) to assess the respondent’s self-rated health status. Only the AQoL will be used as a secondary outcome, the EQ-5D will only be used for sensitivity analyses in the health economic outcome evaluation.

#### Cost measures

The Trimbos and iMTA Treatment Inventory of Costs in Patients with psychiatric disorders (TIC-P) [77] was adapted for the application to the German health care system and the specific target group. Direct medical costs (e.g., drugs), direct non-medical costs (e.g., transportation) and indirect costs (e.g., productivity losses) [78] will be assessed over a period of the previous 3 months. A catalog of German unit costs [79] will be used to calculate total health care costs on individual basis assuming that the majority of participants will be from Germany [80]. Indirect non-medical cost stemming from productivity losses due to presenteeism and absenteeism costs will be assessed with specific modules of the TiC-P. From a student’s perspective a monthly rate that students are paid due to the German Federal Law on Support in Education (BAföG) [81] is assumed covering the general cost for living and education in Germany. The intervention costs are estimated at €150 ($181) per participant. This tariff stems from a health care provider (GET.ON Institute) that offers comparable internet-based interventions. Including German VAT of 19%, interventions costs were €178.50.

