### Economic evaluation

We will perform an economic evaluation from the societal and health provider perspectives that include all relevant costs and outcomes. A cost-effectiveness analysis as well as a cost-utility analysis will be conducted following guidelines from the International Society for Pharmacoeconomics and Outcomes Research (ISPOR) Good Research Practices Task Force Report and the recommendations of the Consolidated Health Economic Evaluation Reporting Standard (CHEERS) [92, 93]. In the cost-effectiveness analyses, symptom-free status via SPS and SIAS will be used as clinical outcome. For cost-utility analyses, quality-adjusted life years (QALYs) will be calculated based on the AQOL-8D. EQ-5D-5L will be used only in sensitivity analyses. We will compare both groups in terms of incremental costs and incremental effects, by calculating the incremental cost-effectiveness ratio (ICER). We will use bootstrapping (*N* = 5000) and 95% confidence intervals in percentiles to test the robustness of the ICER and to quantify the uncertainty surrounding the ratios. The results will be shown in a cost-effectiveness plane and in a cost-effective acceptability curve. Additionally, the robustness of the base-case findings will be tested with a multi-way sensitivity analysis (i.e. ± 50% intervention costs, costs outliers, EQ-5D-5L as alternative instrument to calculate QALYs).

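### With the TiC-P given only at t0 and t2 and a 3-month recall, participant-reported costs in the first three months after randomisation, including the whole 10-week treatment phase, are observed in neither arm

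*Protocol article*

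**What the plan says.** - **Recall.** The Cost measures section lists direct medical, direct non-medical and indirect costs, and says that these "will be assessed over a period of the previous 3 months".
- **Schedule.** In Table 2 (Measurements), the row for the "Trimbos/iMTA Questionnaire for Costs associated with Psychiatric Illness" is ticked at t0 and t2; the t1 cell is empty. The rows for the AQoL-8D and EQ-5D-5L are ticked at t0, t1 and t2. The footnote defines the times as "t0 Baseline; t1 10 weeks; t2 6 months".
- **Timing.** The Procedure section anchors t2 as "follow-up six months after randomization (t2". Intervention participants "can initiate the online-based self-help intervention immediately after randomization", and the post-treatment assessment is placed "immediately after completing the program (t1; 10 weeks".
- **Use.** The Economic evaluation section plans a cost-effectiveness analysis on symptom-free status and a cost-utility analysis on QALYs from the AQoL-8D, from "societal and health provider perspectives that include all relevant costs and outcomes".
- **Intervention cost.** The Cost measures section assigns a tariff of €150 per participant, or €178.50 with 19% VAT. It is not collected through the TiC-P.

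**The concern.** A look-back questionnaire observes only its recall window. With two administrations six months apart and a three-month look-back, half of the time between them is not asked about. Here the unobserved half is the one in which the intervention is delivered.

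That window matters for three reasons. Both arms may use usual care throughout, and controls wait six months for the programme, so early differences between the arms in other care and in productivity are plausible. The tariff is charged in full, while any offsetting saving during treatment goes unseen. And cost-effectiveness is a stated aim: the Background section notes that no health economic evaluation exists for an unguided internet intervention in this disorder.

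The sensitivity analyses listed under Economic evaluation (±50% intervention cost, cost outliers, EQ-5D-5L in place of the AQoL-8D) do not address it.

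**Working it through.** The document states no figure for the costing period, so there is none to reproduce. The check is interval arithmetic on its own times. The one related figure does reproduce: 150 × 1.19 = €178.50.

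**Inputs.** Recall 3 months (Cost measures). TiC-P at t0 and t2 (Table 2). t2 at 6 months after randomisation, treatment from day 0, t1 at 10 weeks = 70 days (Procedure).

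**Windows.** Observed window = [assessment time − recall, assessment time].
- t0 form: [0 − 3, 0] = months −3 to 0, before randomisation.
- t2 form: [6 − 3, 6] = months 3 to 6.
- Observed by neither: months 0 to 3, which is 3/6 = 50% of follow-up.

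**In days.** One month = 365.25/12 = 30.4 days, so 6 months = 182.6 days and 3 months = 91.3 days. Gap = 182.6 − 91.3 = 91.3 days. Treatment occupies days 0 to 70 and so lies wholly inside the gap, with 91.3 − 70 = 21.3 days to spare.

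**Other readings of the calendar.** Taking the recall as 12 weeks, 13 weeks or 91.3 days, and follow-up as 26 weeks or 182.6 days, the gap is about 91 to 99 days, or 50% to 54% of follow-up. The longest is 182.6 − 84 = 98.6 days; 98.6/182.6 = 54%. The treatment phase is inside the gap every time.

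**What each way of handling the gap would do.** Let P be the tariff and c the non-intervention cost per month in an arm.
- *t2 costs unscaled:* if c is constant, the six-month total is 6c and the form records 3c, so the understatement is 6c/3c = 2. The factor applies to non-intervention costs only. The incremental cost would be P + 3(c_I − c_C) instead of P + 6(c_I − c_C), with P counted in full in both.
- *t2 costs doubled:* gives 2 × 3c = 6c, which is correct if use in months 0 to 3 equals use in months 3 to 6.
- *Interpolation from t0 to t2:* the window midpoints are −1.5 and 4.5 months, and the midpoint of the gap is 1.5 = (−1.5 + 4.5)/2. Linear interpolation therefore sets the missing quarter to (C0 + C2)/2, where C0 and C2 are the two recorded three-month costs. If the true cost of that quarter differs by δ, the six-month total is wrong by exactly δ, and no participant-reported cost in the trial estimates δ.

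**Would a t1 form with unchanged recall close the gap?** Not fully. It would cover days −21.3 to 70, and the t2 form covers days 91.3 to 182.6. That leaves 91.3 − 70 = 21.3 days, or 21.3/182.6 = 12%, uncovered. With each recall reaching back to the previous assessment, the windows are 10 weeks and 26 − 10 = 16 weeks, and 10 + 16 = 26 leaves no gap.

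**The case against.** Four objections narrow the point, and they stand.

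1. *A reader might infer that all costs of the first three months are lost.* They are not. The cost certain to differ between the arms in that window, the intervention, enters as a tariff and is varied by ±50%. The gap concerns what participants report.
2. *A reader might infer that the plan understates costs by a factor of 2.* The document states no rule for scaling costs to the follow-up period. The factor arises only if t2 costs are used unscaled and use is constant. Under that same constancy, doubling removes the error. Interpolation from t0 is a third route, and the t0-to-t2 change in each arm gives partial evidence on stability.
3. *A reader might infer that costs and effects cover different periods in both economic analyses.* The mismatch belongs to the cost-utility analysis, where QALYs accrue over time. Symptom-free status is a state at a time point. Even for QALYs, the six-month period is inferred from Table 2, since no horizon is stated.
4. *A reader might infer that the trial's main result is at risk.* Social anxiety symptoms are the primary outcome, and nothing here touches them.

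One objection does not stand: that the scaling rule can be left to an unseen analysis plan. Such a plan can choose how to impute months 0 to 3, but it cannot recover answers to questions that were not asked. Interpolation is also weaker here than usual, because people in psychotherapy at entry are excluded, as are those with a recent dose change in anxiety or depression medication. Costs before entry are therefore selected on current care.

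One caveat on Table 2: its symbol for assessments in the intervention group only is not legible in the available text. If the empty t1 cell held that symbol, intervention participants would have early cost data, but controls would still have none and the arms could not be compared.

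**Conclusion.** The point holds for participant-reported health care use, non-medical costs and productivity losses. About months 0 to 3 after randomisation, 50% of follow-up (50% to 54% across calendar readings) and 100% of the 10-week treatment phase, are observed in neither arm. This conflicts with the commitment to include all relevant costs. In the cost-utility analysis it sets partly unobserved costs against QALYs that can be built over the full six months.

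The resulting bias in the incremental cost cannot be given a size or a sign from the document, because it depends on how use differs between the treatment phase and later, and on a scaling rule that is not stated. The conclusion rests on the recall applying at both administrations as written, on the ticks in Table 2, and on a six-month economic horizon. It should be fixed because the aim is stated and the loss cannot be repaired after data collection. It bears on the economic evaluation only.

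**What to change.** Add the TiC-P to the existing t1 online battery in both arms. Set the t1 recall back to randomisation (about 10 weeks) and the t2 recall back to t1 (about 16 weeks). State in the Economic evaluation section that the costing period equals the QALY period.

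For participants already past t1, use a 6-month recall at t2 in both arms, and check the effect of the mixed recall lengths in a sensitivity analysis.

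The cost is one more self-report form in a web survey that participants already complete, and a t2 recall about three weeks longer than now (16 against 13 weeks). Participants already past t1 face a recall of six months instead of three, with some loss of accuracy. The article already lists self-reported costs as a limitation, and the longer recall should be mentioned there.

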#### Other measures

Other assessments will include demographic variables (e.g., age, gender, student status, etc.). Moreover, a version of the German Client Satisfaction Questionnaire (CSQ-8) [82] that was adapted to the online training context will assess the acceptance of internet-based interventions and global client satisfaction on the intervention [83]. Adherence to treatment will be evaluated by completion rate and time spent in intervention. The 6-item German version of the Credibility Expectancy Questionnaire (CEQ) [84] assesses the intervention’s credibility and outcome expectancies. Additionally, credit points based on the European Credit Transfer System (ECTS) [85] are assessed to evaluate the reduced academic productivity.

#### Process measures

Participants in the active conditions will be asked to rate their symptoms of SAD every two weeks (SPS & SIAS) in order to detect change in social phobic symptoms during the intervention.

### Power and sample size calculation

The study is powered to detect small to medium effect sizes of d = 0.4. The intended sample size of 200 participants will provide sufficient power to detect a significant standardized effect size (Cohen’s d) of 0.4 on the primary outcome variable (symptoms of SAD via SPS and SIAS) between the two conditions. The software Gpower [86] was used to calculate the sample size of *n* = 100 per group given a Bonferroni-adjusted (due to multiple testing) alpha error level of 0.025 for a one-sided test, a statistical power of 0.80 and an effects size of d = 0.4.

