### Randomization

Two hundred participants will be randomly assigned. The allocation list is produced by a random number generator Randlist [9] which randomly allocates participants in a 1:1 ratio with a block size of 8 to either IMI or WLC. The list is operated by an independent researcher not otherwise involved in the study. This researcher has no information about the participants other than the participants’s trial ID numbers and will randomize the participants in the order of the incoming informed consent form. During the randomization process, the allocation will be concealed from participants and researchers involved in recruitment. Participants will not be blinded to study conditions.

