### Analysis

Analyses will be conducted and reported according to the Consolidated Standards of Reporting Trials (CONSORT) statement [87]. The results will be disseminated in peer-reviewed scientific journals. The depersonalized data will be analyzed based on the intention-to-treat principle. Missing data will be handled using multiple imputations with 10 estimations per missing value following recommendations of Little and Rubin [88] and Schafer [89]. Differences in continuous outcomes between the groups will be analyzed using analysis of covariance (ANCOVA), with pre-scores as a covariate and the post-scores as the dependent variable. Possible confounders (e.g. former use of psychotherapy) will be assessed and included as covariates if they should be associated with changes in the primary outcome. We will compute standardized effect sizes (Cohen’s d including the 95% confidence intervals for all effect sizes). We will also test differences in treatment response rates (50% relative symptom reduction), numbers of participants displaying reliable change (according to Jacobson and Truax [90]) as well as differences in symptom deterioration rates. Effect sizes between groups of dichotomous outcome variables will be expressed as number needed to treat and its associated 95% confidence intervals. All reported *p*-values are (one-sided) at a significance level of 0.025 for the primary outcomes and 0.05 for the secondary outcomes.

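### Replacing the fixed Bonferroni split across SPS and SIAS with a Holm step-down would cost one sentence and gain power at the same family-wise bound; the present rule is valid

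*Protocol article*

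**What the plan says.** The Primary outcome measures section of the protocol article gives one primary construct with two instruments: "SAD symptoms will be measured with two widely used measures", the SPS and the SIAS. Table 2 lists both under the primary outcome, and the Abstract places the primary comparison at post-treatment (t1, 10 weeks).

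The Power and sample size calculation section sets a "Bonferroni-adjusted (due to multiple testing) alpha error level of 0.025 for a one-sided test", with "a statistical power of 0.80 and an effects size of d = 0.4", and arrives at 100 per group. It describes this as power "on the primary outcome variable (symptoms of SAD via SPS and SIAS) between the two conditions".

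The Analysis section repeats the level: p-values are "one-sided) at a significance level of 0.025 for the primary outcomes and 0.05 for the secondary outcomes". Neither section describes a step-down or any passing on of alpha. Neither says whether one significant scale is enough or both are needed, and the article gives no SPS-SIAS correlation.

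**The concern.** A fixed split holds the second scale to 0.025 even after the first has been rejected. The Holm procedure releases the full family level to the second scale at that point and keeps the same bound on the family-wise error. Every result that Bonferroni declares significant, Holm also declares significant, and sometimes it declares one more. As a testing rule the fixed split therefore gives power away.

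A smaller point concerns the label on the power figure. The 80% is attached to the primary outcome in the singular, with both scales in brackets, but the calculation delivers 80% for one scale tested alone. It is not the chance of confirming both scales, nor of confirming at least one. The article says that the two scales complement each other, so a reader may well want to know the chance of a result on both.

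**Working it through.** **Inputs from the article.** d = 0.4 (SD 1), 100 per group, 1:1 allocation, one-sided 0.025 per scale (implied one-sided family level 2 × 0.025 = 0.05), power 0.80.

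**Assumptions.** SPS-SIAS correlation ρ = 0.6, range 0 to 0.9. The effect is 0.4 on both scales, all 200 are analysed, and baseline adjustment adds no precision.

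**1. The plan's own figure.** Normal approximation: n = 2 × (1.960 + 0.842)² / 0.4² = 98.1, so 99 per group. With the t-test, power is 0.7997 at 99 and 0.804 at 100 per group, so 100 is needed. The stated sample size reproduces for a single scale.

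**2. Power for one scale.** The test statistic has mean 0.4 × √(100/2) = 2.83. Power at 0.025 is Φ(2.83 − 1.96) = 0.807. At 0.05 it is Φ(2.83 − 1.645) = 0.882.

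**3. Both scales.** Take (Z1, Z2) as bivariate normal, each with mean 2.83, and correlation ρ.

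- Bonferroni, both = P(Z1 > 1.96, Z2 > 1.96)
- Holm, both = P(larger > 1.96 and smaller > 1.645) = 2 × P(Z1 > 1.96, Z2 > 1.645) − P(Z1 > 1.96, Z2 > 1.96)

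Hand check at ρ = 0: Bonferroni 0.8074² = 0.652; Holm 2 × 0.8074 × 0.8817 − 0.652 = 0.772.

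| ρ (assumed) | Both, Bonferroni | Both, Holm | Each scale, Holm | At least one, either rule |
|---|---|---|---|---|
| 0 | 65.2% | 77.2% | 86.7% | 96.3% |
| 0.3 | 67.7% | 78.4% | 86.1% | 93.8% |
| 0.5 | 69.7% | 79.6% | 85.7% | 91.8% |
| 0.6 | 70.9% | 80.2% | 85.4% | 90.6% |
| 0.7 | 72.2% | 81.0% | 85.1% | 89.2% |
| 0.9 | 75.9% | 82.7% | 84.1% | 85.6% |

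At least one = 2 × 0.807 − both (Bonferroni). Each scale under Holm = (at least one + both under Holm) / 2; under Bonferroni it is 80.7% throughout. Simulated t-tests with 100 per group agree: 69.3% and 79.3% at ρ = 0.5, 71.7% and 80.8% at ρ = 0.7.

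**4. Error rate.** If neither scale has an effect, the two rules have the same family-wise error: 0.05 − P(both > 1.96 under the null) = 4.4% at ρ = 0.6. If only one scale has an effect, Holm's error on the other can rise from 0.025 towards 0.05, which is still within the family bound.

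**5. Sensitivity of the levels (both scales, Bonferroni to Holm).**

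- With 80 analysed per group and ρ = 0.7: 61% to 71%.
- With baseline adjustment, an assumed pre-post correlation of 0.5, d = 0.4 on the raw SD and ρ = 0.7: 85% to 91%.

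The levels move a good deal, but Holm is never lower.

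**The case against.** The case for leaving the plan alone is substantial.

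- **Nothing is miscalculated.** Bonferroni controls the error, the two sections agree on 0.025 one-sided, and n reproduces. This stands: the point is about efficiency.
- **No section requires both scales to be significant.** A reader might infer from the complementary scales that success means an effect on both, and that the trial is therefore underpowered for its aim. The article does not say so. An alpha split fits a plan in which either scale can support its own claim, and for at least one scale Holm adds nothing. If both were truly required, no split would be needed: testing each at the full 0.05 would give 81.2% at ρ = 0.6, slightly more than Holm.
- **A both-scale power below 80% is not established.** The planned analysis is ANCOVA on the pre-score. With ρ = 0.6, no dropout and d = 0.4 on the raw SD, both-scale power under plain Bonferroni is 79.5% at an assumed pre-post correlation of 0.4 and 84.5% at 0.5. The article gives no such correlation, so a shortfall can be neither claimed nor excluded.
- **The fixed rule matches the intervals.** A one-sided 0.025 test agrees with the lower limit of the two-sided 95% interval that the Analysis section promises for effect sizes. Holm loses that match for the second scale. This is a real cost, though a small one.
- **The 80% can be read as per test**, because the adjusted level is named beside it. That is fair for a statistician, but the sentence still attaches it to the two scales together.

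**Conclusion.** The point holds as a cheap improvement. The plan's multiplicity rule is valid and its sample size is correct for one scale, but Holm has higher power at the same implied one-sided 0.05 family-wise bound. Under the plan's inputs the gain in confirming both scales is about 9 percentage points at an assumed correlation of 0.6, and about 7 to 12 points over 0 to 0.9. Per scale it is about 3 to 6 points. The direction does not depend on the assumed correlation, the ANCOVA gain or dropout, but the absolute levels do. The documents do not support a conclusion that alpha is wrong, that the sample size is wrong or that the trial lacks power for a stated objective.

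**What to change.** In both the Power and sample size calculation section and the Analysis section, replace the fixed split with wording such as:

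> SPS and SIAS at t1 are tested by the Holm procedure. The smaller p-value is compared with half the family level; if it is significant, the other is compared with the full family level. A claim is made for each scale that is rejected.

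In the power section, label the 80% as power per scale. If power for both scales is added, state the assumed correlation and its range beside it.

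The cost is a sentence in each section, with no extra participants or data. Two consequences should be accepted openly. The second scale may be significant at one-sided 0.05 while its two-sided 95% interval includes zero, so the report should say that the intervals are not adjusted to the step-down. A scale with no effect can also carry an error of up to 0.05 when the other scale has one. A team that values exact agreement between test and interval could reasonably keep Bonferroni and change only the power label.
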